##### Anxiety and depression scores

Anxiety severity will be measured by the Beck Anxiety Inventory (BAI), a 21-item tool, in which each item is rated on a 0 to 3 point scale, resulting in a total score between 0 to 63, with ≥30 indicating severe anxiety [34]. This tool is reported to have a good reliability [39] and validity [40].

The Anxiety Sensitivity Index (ASI) is a 16-item questionnaire for measuring anxiety sensitivity. Each item is rated on a 5-point Likert scale with scores from 0 (barely) to 4 (very much), with a total score ranging from 0 (no anxiety sensitivity) to 64 (severe anxiety sensitivity) [41]. The ASI is a reliable measure [42]. Anxiety sensitivity has been found to be a predictor for relapse in patients with remitted anxiety disorders [3].

The Inventory of Depressive Symptomatology – self-report (IDS-SR) is a 30-item questionnaire for measuring severity of depressive symptoms [35]. Each item is rated on a 0 to 3-point scale, and by summing 28 of the 30 items the total score ranges from 0 to 84, with ≥39 indicating severe depressive symptoms. The questionnaire has highly acceptable psychometric properties [43].

Anxiety and mood data are also collected in the weekly diary. Mood is measured by asking ‘how would you rate your mood today?, from 1 (very sad) to 10 (very happy)’. Anxiety is measured by asking ‘how would you rate the intensity of anxiety today?, from 1 (very relaxed) to 10 (very anxious/tense)’.

##### Functioning

General functioning and disability will be measured using the World Health Organization Disability Assessment Schedule 2.0 (WHODAS 2.0). This 36-item tool measures six domains: cognition, mobility, self-care, getting along, life activities and participation. Each item is rated on a 5-point Likert scale with scores from 0 (no difficulty) to 4 (extreme difficulty or cannot do). By using the ‘item-response theory’-based scoring, the scores will range from 0 (no disability) to 100 (full disability) [44]. The WHODAS 2.0 is reported to have strong psychometric properties [45].

##### Healthcare use

Healthcare and medication use will be measured using an adjusted version of the Trimbos/iMTA Questionnaire for Costs Associated with Psychiatric Illness (TiC-P). Only psychotropic medication will be registered. Health care use is measured as the number of contacts with different healthcare providers. The TiC-P is a feasible and reliable instrument for measuring healthcare use and costs [46].

##### Satisfaction with the relapse prevention programme

Satisfaction with the relapse prevention programme will be assessed using the ‘Satisfaction with treatment measure’. This 14-item measure provides insight into overall satisfaction, how helpful and useful patients valued the programme, perceived support and effect [47]. Also patients will be asked to rate each online module. The original scale was translated into Dutch by the authors, with permission of the author.

#### Quantitative data analysis

For each of the quantitative research questions, a separate analysis will be performed using log data from the E-health platform, data from the case registration forms that have been completed by the MHPs, and data from the four questionnaires:To what extent do patients use a tailored relapse prevention programme?

The use of the tailored relapse prevention programme will be described, focusing on different aspects of its use, such as the number of login sessions, the amount of time spent online, the number of completed modules, the number of diary entries, the number of sessions and the number of online and face-to-face conversations with the MHP. Descriptive statistics will be used to provide insight into these aspects of the use of the relapse prevention programme.2)What factors influence the use of the programme?

The use of the tailored relapse prevention programme may differ across patients, and may depend on age, education level and clinical situation. We will explore possible differences in usage between groups of patients systematically, considering sociodemographic factors, clinical symptoms and self-management strategies.3)What is the association between usage intensity and course of symptoms?

Descriptive statistics will be used to provide insight into course of symptoms for ‘high-use’ participants and ‘low-use’ participants. In order to analyse the association between usage intensity and course of symptoms, multiple regression analyses will be performed. We will first analyse the change in anxiety severity from baseline to follow-up (9 months) with the following independent variables: intensity of E-health use, number of diary entries and number of contacts with the MHP. We will repeat these analyses for the depression outcomes. In addition, analyses will be performed using ‘deterioration: yes or no’ as outcome variable. Deterioration is defined as an increase of 1 standard deviation on the IDS-SR and/or on the BAI. The standard deviation will be calculated using data from the NESDA study [48], the study from Kok et al. [49], and the present study. This analysis will be performed using a time-lag model, in which the outcome will be assessed using determinants from an earlier measurement (deterioration at time_*t*_ predicted by usage intensity at time_*t-1*_), since we assume that usage intensity might influence whether deterioration occurs at a later point in time.

Because of the observational nature of the data, it will be difficult to draw conclusions about the effects of the relapse prevention programme. However, we will conduct additional explorative analyses to estimate the association between usage intensity and course of symptoms. All data analysis will be performed using SPSS statistical analysis software.

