### Setting

This study will be performed in two settings:General practices throughout the Netherlands, with the participation of approximately 50 MHPs. Patients follow the programme at home via an E-health platform, accompanied by face-to-face contact with the MHPs.Ambulatory mental healthcare services with the participation of eligible patients whose GP is not willing to participate in this study. A trained MHP will deliver the relapse prevention programme using the same protocol as in the participating general practices.

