#### Recruitment via mental healthcare services

Patients who completed their treatment and are recruited via mental healthcare services, will be contacted by the researchers directly. These patients will be supported during the GET READY programme by a MHP working in the ambulatory mental healthcare.

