#### Sample size

In order to determine the sample size, we assumed a moderate effect (*r* = 0.24 that corresponds to Cohen’s *d* = 0.5) of the intensity of programme use (*X*) on the change in symptoms of anxiety and depression (*Y*). Since this is a non-randomized study, we will use a set of covariates ***W*** to correct for selectivity in the uptake of the programme. In applying the G*Power 3 software [50] to determine the sample size, we assume that the effect of *X* corresponds to a 6% of explained variance of *Y* (equivalent to the moderate effect, since *R*^2^ = *r*^2^ = 0.24^2^ = 0.06) above the covariates ***W*** and assume a 6% reduction of the total variance in *Y* of the residual variance due to the use of covariates of ***W***, leading to a partial *R*^2^ = 0.06 or, equivalently, an effect size of *f*^2^ = 0.0638. Furthermore, setting *α* = 0.05 and the power of 1 – *β* = 0.80, the sample size calculation shows that 126 patients are needed. Patients will be considered as drop-out when they refuse to complete questionnaires. With an estimated attrition of 20% (i.e. 80% complete at least one follow-up questionnaire), we aim to include 158 patients.

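### The research question 3 regression makes no allowance for patients sharing a mental health professional and does not name setting; the likely effect is small, but the ambulatory caseload is left open

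*Protocol article*

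**What the plan says.** Under Quantitative data analysis, research question 3, the article states that "multiple regression analyses will be performed" for the change in anxiety from baseline to 9 months, "with the following independent variables: intensity of E-health use, number of diary entries and number of contacts with the MHP". The same is repeated for depression, and a time-lag model is added for deterioration. No random effect, robust standard error or setting term is mentioned. For research question 2, usage is to be explored "considering sociodemographic factors, clinical symptoms and self-management strategies", which are all patient-level factors.

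Under Sample size there is a further commitment: "Since this is a non-randomized study, we will use a set of covariates" (called **W**) "to correct for selectivity in the uptake of the programme". Its members are not listed. The calculation arrives at 126 analysed and 158 enrolled patients without a design effect.

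On structure, Setting describes "General practices throughout the Netherlands, with the participation of approximately 50 MHPs", and a second setting, ambulatory mental healthcare, for "eligible patients whose GP is not willing to participate in this study". Recruitment via mental healthcare services says of patients recruited by that route: "These patients will be supported during the GET READY programme by a MHP working in the ambulatory mental healthcare". It does not repeat the condition about the GP. Role of MHP says that patient and MHP settle the frequency and number of contacts together, and that the MHP can support use of the online programme.

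**The concern.** A regression that treats patients as independent gives standard errors that are too small when both the predictor and the outcome are correlated within MHP. One of the three predictors is the number of contacts with the MHP, so some clustering of that predictor is to be expected from the design. Online use may cluster as well, though less. Outcomes may cluster if MHPs differ in skill or in the patients they see.

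Setting raises a separate question. The two groups reach the study by different routes: MHPs search their own files in general practice, whereas researchers contact patients directly in mental healthcare services. If the settings differ in both usage and symptom course, part of that difference would appear as a usage–symptom association.

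At stake are the tests and intervals for the usage coefficients, which is the association the study is powered on.

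**Working it through.** **Reproducing the plan's figure.** Partial R² = 0.06 gives f² = 0.06/0.94 = 0.0638. An F test of one predictor at α = 0.05 with noncentrality f²·N reaches power 0.803 at N = 126. Then 126/0.80 = 157.5, so 158. Both stated figures reproduce, and they assume independent patients.

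**Inputs for the clustering check.**
- From the documents: about 50 MHPs, 126 analysed patients, f² = 0.0638.
- Assumed, because the documents give none: outcome ICC 0.05 or 0.10; usage ICC 0.3, or 1.0 as the limit in which usage is wholly determined by the MHP.
- Average cluster size m = 126/50 = 2.52. The analysed number is used because the 80% power belongs to it.

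**Even caseloads.** For a regression slope, DE = 1 + (m − 1) × ICC(outcome) × ICC(usage). The effective N is 126/DE, and the actual two-sided α is 2[1 − Φ(1.96/√DE)].

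| Outcome ICC | Usage ICC | DE | Effective N | Actual α | Power |
|---|---|---|---|---|---|
| 0.05 | 0.3 | 1 + 1.52 × 0.015 = 1.023 | 123 | 0.053 | 0.79 |
| 0.05 | 1.0 | 1 + 1.52 × 0.05 = 1.076 | 117 | 0.059 | 0.77 |
| 0.10 | 1.0 | 1 + 1.52 × 0.10 = 1.152 | 109 | 0.068 | 0.745 |

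In the first row the standard error is understated by about 1% (1/√1.023 = 0.989).

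**Uneven caseloads.** This formula does not suit a design with a few dominant clusters, so type I error was simulated: ordinary least squares, no true effect, N = 126 and 158, usage ICC 0.3–0.5, 10,000 runs per case. At nominal 5%:
- even caseloads, outcome ICC 0.05–0.10: 5.3–6.3%
- one MHP with 30 patients, outcome ICC 0.10: 6.6–7.5%
- one MHP with 60 patients, outcome ICC 0.10: 7.9–9.9%
- three MHPs with 25 patients each, outcome ICC 0.10: 8.0–10.7%

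At outcome ICC 0.05, the three uneven cases give 5.7–8.3%.

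**Setting.** The documents give no split between settings and no difference in usage or outcome, so only an illustration is possible. Suppose 60 of 126 patients are ambulatory and differ by d within-setting standard deviations in both usage and change. The spurious correlation is r = p(1 − p)d²/[1 + p(1 − p)d²], with p(1 − p) = (60/126)(66/126) = 0.249.
- d = 0.5: r = 0.0624/1.0624 = 0.059. The shift is 0.059 × √126 = 0.66, and type I error is about 10%.
- d = 0.3: r = 0.0224/1.0224 = 0.022, and type I error is about 6%.

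**Who is in the ambulatory setting.** Setting limits it to patients whose GP declines. Recruitment via mental healthcare services assigns to it the patients who come by that route, with no such limit. The two readings imply different ambulatory caseloads, and caseload is what decides which simulated case applies.

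**The case against.** The strongest reply has four parts.

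1. **The covariate set.** **W** is meant to correct for selective uptake and may include setting. An article can leave its members to an analysis plan that is not shown. This stands: a reader might infer that the plan ignores setting, and the documents do not establish that. They show only that setting is not named. **W** would not, however, deal with correlation within MHP.

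2. **Confounding is not shown.** A reader might also infer that setting does confound usage. No figure in the article supports that, and Setting says that the ambulatory MHP follows the same protocol as the general practices. Confounding is plausible only.

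3. **Usage is largely the patient's own.** Patients choose optional modules by preference, feedback is given when they ask for it, and contacts are agreed jointly. Online intensity and diary entries are patient behaviours. This stands against the usage ICC of 1.0, which is a limit and not an expectation. It does not remove the MHP's part in the number of contacts.

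4. **Small effect, modest claims.** With even caseloads the error rate is close to nominal, so a flat statement that standard errors are too small goes further than the documents allow. The article also says that conclusions about effects will be difficult, and its Discussion says the design does not suit an efficacy question. Both remarks lower the priority. The caveat about effects concerns causal reading, though, and does not make an understated standard error correct.

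**Conclusion.** The point holds in a limited form. As stated, the research question 3 model has three usage predictors and no allowance for shared MHPs, and the sample size has none either. Standard errors may be too small and setting may confound the association; neither is demonstrated.

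The size depends on ICCs and caseloads that the documents do not give. Under moderate assumptions and even caseloads it is negligible. If usage were wholly MHP-determined, power would fall from 0.80 to about 0.77 at outcome ICC 0.05 and about 0.75 at 0.10. With usage ICC at 0.3–0.5 and outcome ICC 0.10, error rates near 8–10% require a few ambulatory MHPs to carry large caseloads, which the present text neither states nor rules out. This is a minor point, worth making because the remedy is cheap.

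**What to change.** - Fit the research question 3 models with a random intercept for MHP. If a few MHPs turn out to have very large caseloads, this is preferable to clustered standard errors.
- Name setting (general practice or ambulatory mental healthcare) as a member of **W**, and say that **W** enters the research question 3 models.
- Reconcile Setting with Recruitment via mental healthcare services on which patients are supported by the ambulatory MHP, since that determines caseload.

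The cost is a few sentences of analysis text and slightly wider intervals. No new data are needed: the MHP completes a case registration form after each face-to-face contact, and setting follows from where the patient is supported.

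### The regression for research question 3 lists only usage variables, without the covariates W that the sample size assumes or the baseline score, so the association is open to confounding and regression to the mean

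*Protocol article*

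**What the plan says.** Two sections of the protocol article describe the analysis of research question 3, the association between usage intensity and course of symptoms.

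- **Quantitative data analysis.** The outcome is the change in anxiety severity between baseline and nine months, analysed by multiple regression "with the following independent variables: intensity of E-health use, number of diary entries and number of contacts with the MHP". The analysis is repeated for depression. A further analysis takes deterioration (yes or no) as outcome in a time-lag model with earlier usage as determinant. No covariate and no baseline score is named for any of these.
- **Sample size.** "Since this is a non-randomized study, we will use a set of covariates" W "to correct for selectivity in the uptake of the programme". The effect of usage X on symptom change is defined as variance explained above W, with partial R² = 0.06 and "an effect size of *f*^2^ = 0.0638". With "setting *α* = 0.05 and the power of 1 – *β* = 0.80" this gives 126 evaluable patients, and 158 after 20% attrition.

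Under research question 2, the Quantitative data analysis section also says that use "may depend on age, education level and clinical situation". The end of that section and the Discussion caution that the observational design does not allow conclusions about efficacy.

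**The concern.** The model that was powered tests usage above W. The model described in the analysis section has no W. An analyst who follows the explicit predictor list would fit an unadjusted model, and the correction for selective uptake would be lost.

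This matters because the article expects usage to be selective. Patients choose optional modules by their own preferences and goals, contact frequency is agreed individually with the mental health professional, and patients in full and in partial remission are both enrolled. Usage may therefore follow residual symptoms. A raw change score is negatively related to its own baseline through regression to the mean. If more symptomatic patients use the programme more, part of their expected fall in score would be credited to usage. If heavier users are the less symptomatic ones, the bias reverses and could hide a benefit.

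**Working it through.** **1. Reproducing the article's figure.** Inputs from Sample size: partial R² = 0.06, α = 0.05, power 0.80, attrition 20%.

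- f² = 0.06 / (1 − 0.06) = 0.0638, as stated.
- Test of one predictor among p in total: noncentral F with 1 and N − p − 1 degrees of freedom, noncentrality λ = f² × N. At N = 126, λ = 0.0638 × 126 = 8.04.
- Power at N = 126 is 0.803 with 3 to 10 predictors in total and 0.802 with 15 to 20. The smallest N that reaches 0.80 is 125 or 126 over this range.
- 126 / 0.80 = 157.5, rounded up to 158.

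The stated 126 and 158 reproduce as a test of one usage variable. They do not depend materially on how many covariates are in the model.

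**2. The two sections side by side.**

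| | Sample size | Quantitative data analysis |
|---|---|---|
| Outcome | change in symptoms | change in anxiety (then depression) to nine months |
| Usage | X | three usage measures |
| Covariates W | included, to handle selective uptake | not listed |
| Baseline score | not stated (may be meant within W) | not listed |

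W is mentioned nowhere outside the Sample size section.

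**3. Illustration of what omitting baseline could do.** The article gives neither correlation needed, so these are assumptions: baseline-to-nine-month correlation ρ = 0.4 to 0.7; usage–baseline correlation r = 0.1 to 0.3; equal SDs at both times; no usage effect given baseline; one usage measure for simplicity.

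- With unit SDs, Y9 = ρY0 + e, so change = (ρ − 1)Y0 + e, with variance 2(1 − ρ).
- Spurious correlation of usage with change = −r × √((1 − ρ)/2).
- Rejection rate at N = 126: noncentral F with 1 and 124 degrees of freedom, λ = N × c²/(1 − c²), where c is the spurious correlation.
- Example, ρ = 0.6 and r = 0.3: c = −0.3 × √0.2 = −0.134; λ = 126 × 0.018/0.982 = 2.31; rejection rate 33%.

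| ρ | r = 0.1 | r = 0.2 | r = 0.3 |
|---|---|---|---|
| 0.4 | −0.055 (9%) | −0.110 (23%) | −0.164 (46%) |
| 0.5 | −0.050 (9%) | −0.100 (20%) | −0.150 (39%) |
| 0.6 | −0.045 (8%) | −0.089 (17%) | −0.134 (33%) |
| 0.7 | −0.039 (7%) | −0.077 (14%) | −0.116 (26%) |

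The nominal rate is 5% and the planned effect is r = 0.24.

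**4. The opposite assumption.** Suppose instead that heavier users differ stably in severity and all patients change in parallel, so that usage correlates r with both Y0 and Y9. The change score is then unrelated to usage and holds 5%. The baseline-adjusted model has a spurious partial correlation of r(1 − ρ)/√((1 − r²)(1 − ρ²)). With ρ = 0.6:

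- r = 0.2: 0.08/√(0.96 × 0.64) = 0.10, rejection rate 21%.
- r = 0.3: 0.12/√(0.91 × 0.64) = 0.16, rejection rate 43%.

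Which model is biased therefore depends on an assumption that the data cannot test.

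**The case against.** The strongest defence is that adjustment is already planned. The Sample size section commits to W, and the predictor list in the analysis section does not say that it is exhaustive. Read together, one section gives the exposures and the other the adjustment. Naming the members of W is a detail that an article may leave to the full plan, and baseline severity could be among them. The choice between a change score and baseline adjustment in a non-randomised cohort is also a known dilemma (Lord's paradox), as step 4 of the working shows. Finally, the article disclaims efficacy conclusions and treats this as one of five questions.

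Much of this stands. It would be wrong to say that adjustment was never intended, that the change score is always the biased analysis, or that the association is shown to be confounded. The remark that "Anxiety sensitivity has been found to be a predictor for relapse in patients with remitted anxiety disorders" supports the anxiety sensitivity score (ASI) as a prognostic covariate, but it says nothing about usage and does not demonstrate confounding.

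The defence does not remove the mismatch. The regression is the one place where the predictors are listed, and W is absent from it. The promised additional explorative analyses name no covariates either. Research question 3 is a stated aim, the sample size rests on it, and the Discussion still expects insight into how usage influences symptoms.

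**Conclusion.** The point holds at moderate severity. The regression as described is not the one the study was sized for, and followed literally it leaves the association open to confounding and regression to the mean. Under the assumptions in step 3 the false-positive rate would be about 7–46%. That range illustrates the risk and does not estimate it: it needs a link between usage and baseline severity, which the article treats only as possible, and it needs the null of no usage effect given baseline.

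A reader might make two stronger inferences. The first is that the change-score model is simply wrong and baseline adjustment right; step 4 shows that the reverse can hold. The second is that adding baseline would raise power above 80%. For ρ = 0.5 to 0.7, baseline adjustment cuts the variance of a change score to (1 + ρ)/2 = 0.75 to 0.85 of its size, and applying this to the planned effect would suggest 86–90%. But the article's 80% already refers to a partial effect above W, which may include baseline, so no gain is established.

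**What to change.** In Quantitative data analysis, state the model for each outcome scale (BAI, IDS-SR) as the usage variables plus:

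- the baseline value of that scale;
- a prespecified W drawn from the T0 variables in Table 2: demographic and clinical variables, self-management score and ASI.

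With baseline in the model, taking change or the nine-month score as outcome gives the same usage coefficients. Recruitment setting is not in Table 2; if it is wanted in W, it has to be taken from recruitment records.

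Use the same adjustment in the deterioration analysis, and cross-refer to W as used in Sample size. Report the W-adjusted change-score model without baseline as a sensitivity analysis, and say that the two models rest on different untestable assumptions. Fix W before the outcome data are analysed.

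The cost is wording only. The Table 2 covariates are already collected at baseline, and for the test of one usage variable at the stated partial effect the numbers remain 126 evaluable and 158 recruited.
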